### Assignment of Interventions

#### Allocation

The research coordinator will register the participants using an electronic data capture system (HOPE eACReSS version 5; Fujitsu). Sequences will be generated by this system before the patients begin the trial (ie, allocation concealment by central registration). The allocation staff will set the audio track (inaudible high-frequency sounds vs placebo sounds) in accordance with the generated sequences. Block randomization without stratification will be used.

#### Masking

All therapists, patients, evaluators, statisticians, and research coordinators will be masked to the allocation. Masking will be checked using the modified version of the Independent Evaluator Knowledge of Outcome^46^ assessment, which was successfully used in a large-scale clinical trial involving CBT.^47^ Using the data, we will calculate the blinding index.^48^

### Data Collection, Management, and Analysis

The Table shows an overall description of the assessment during each visit. Assessment tools include the SHAPS, the SHAPS-C, the GRID-Hamilton Rating Scale, and the Beck Depression Inventory-II.

**Table. zoi190599t1:** Study Measures and Points

Outcome	Tool	Method	Enrollment			Intervention								After Intervention	Follow-up
			Visit 1	Visit 2	Visit 3	Visit 4	Visit 5	Visit 6	Visit 7	Visit 8	Visit 9	Visit 10	Visit 11	Visit 12	Visit 13
Week	NA	NA	−2	−1	0	1-11								12	21
Diagnosis	MINI	IE		X											
Primary outcome, anhedonia	SHAPS	PSR		X		X	X	X	X	X	X	X	X	X	X
Key secondary outcome, anhedonia	SHAPS-C	IE		X										X	X
Other outcomes															
Depression and anhedonia	GRID-HAMD	IE		X										X	X
	BDI-II	PSR			X					X				X	X
Secondary outcomes															
Emotion	PANAS	PSR			X	X	X	X	X	X	X	X	X	X	X
Life satisfaction	SWLS	PSR			X					X				X	X
Well-being	PWB	PSR			X					X				X	X
Treatment mechanisms															
Anhedonia	EROS	PSR			X					X				X	X
Anhedonia	EEfRT	PSR		X										X	X
Safety	AE	TSR and EA				X	X	X	X	X	X	X	X	X	X
Adherence	HCS	TSR					X	X	X	X	X	X	X		
Blinding	IEKNO	PSR, TSR, and EA				X								X	X

Abbreviations: AE, adverse event; BDI-II, Beck Depression Inventory-II; EEfRT, Effort-Expenditure for Rewards Task; EROS, Environmental Reward Observation Scale; EA, evaluator assessment; GRID-HAMD, GRID-Hamilton Depression Rating Scale 17 Item; HCS, Homework Compliance Scale; IE, interview with evaluator; IEKNO, Independent Evaluator Knowledge of Outcome; MINI, Mini-International Neuropsychiatric Interview version 7.0.2; NA, not applicable; PANAS, Positive and Negative Affect Schedule; PSR, participant self-report; PWB, Psychological Well-being Inventory; SHAPS, Snaith-Hamilton Pleasure Scale; SHAPS-C, Snaith-Hamilton Pleasure Scale, clinician administered; SWLS, Satisfaction With Life Scale; TSR, therapist self-report.

#### Primary Outcome

The SHAPS is a 14-item self-report questionnaire used to assess the presence and severity of anhedonia.^40,49^ Each item is answered by different 4-point Likert anchors. Following methods used in previous studies,^50,51^ the total score will be used. A higher score implies more severe anhedonia symptoms, and a total score greater than 20 is interpreted as having anhedonia. Importantly, the reliability of the Japanese version of the SHAPS has been demonstrated (ie, α = 0.90).^49^

#### Key Secondary Outcome Measure

The SHAPS-C offers improved instructions and anchors compared with the original SHAPS.^41^ Similar to the SHAPS, the SHAPS-C consists of 14 items on a 4-point Likert scale. The SHAPS-C has been reported to have sufficient reliability (α = 0.90) and validity (concurrent validity with SHAPS, *r* = 0.85; *P* < .001).^41^ We translated the English version of the SHAPS-C to Japanese using a rigorous back translation procedure.^52,53^

#### Measures of Eligibility, Other Outcomes, Treatment Mechanisms, and Treatment Processes

The Mini-International Neuropsychiatric Interview^34^ will be used to assess eligibility. The GRID-Hamilton depression rating scale,^33,54,55^ Beck Depression Inventory-II,^56^ Positive and Negative Affect Schedule,^57^ Satisfaction With Life Scale,^58^ and Psychological Well-being Inventory^59^ will be used to evaluate the other outcomes. The Environmental Reward Observation Scale^42^ and Effort-Expenditure for Rewards Task^43^ will be used to assess treatment mechanisms, and the Homework Compliance Scale^60^ will be used to assess treatment adherence. Detailed information on these assessments appears in Supplement 1.

#### Statistical Analysis

##### Outcome Analysis

A mixed model for repeated-measures analysis will be conducted to analyze the primary outcome. The dependent variables in this model will be the participants’ SHAPS scores, assessed during 8 visits from weeks 1 to 11 (ie, intervention period) and at week 12 (ie, postintervention period). The fixed effects will be allocation, visit, allocation-by-visit interaction, and SHAPS score before the intervention (ie, week 0). Covariance will be specified as the unstructured structure. The treatment effects will be presented as the difference in adjusted means between the allocations at week 12 (ie, visit 12). The confidence interval will be estimated, and a *t* test will be conducted to determine the effects of treatment. The treatment effect at other weeks as well as the standardized treatment effect will also be analyzed. As a secondary outcome analysis, analysis of covariance, including baseline measures, will be conducted to test the intervention effects on SHAPS-C scores at week 12. The mixed model for repeated-measures analysis will be conducted for the other outcomes. Statistical significance will be set at *P* < .05, and all tests will be 2-tailed.

##### Analysis Population and Missing Data

The primary and secondary outcome analyses will be evaluated using the intent-to-treat principle. Our secondary outcome analysis will use all registered participants who do not meet the discontinuation criteria, as per the protocol set. The mixed model for repeated-measures analysis will be used to treat missing data. Details of the statistical analyses, including interim analysis and stopping guidelines, are described in the statistical analysis plan and trial protocol (Supplement 1).

### Monitoring

#### Data Monitoring

The primary investigator, in collaboration with the research coordinator and data manager, will conduct on-site and central monitoring and will report the results to the members of the data and safety monitoring board. All registered cases will be subjected to central monitoring. On-site monitoring will be conducted for the first 3 registered cases, then for 3 random, preidentified cases thereafter.

#### Adverse Events

Adverse events will be assessed using the Common Terminology Criteria for Adverse Events.^61^ These include dry mouth, astriction, dysuria, vision dysregulation, orthostatic hypotension, sleepiness, fatigue, sleeplessness, anxiety or agitation, depression or anhedonia, lack of appetite, gain or loss of body weight, loss of sexual desire, palpitations, thrill, diaphoresis, headache, dizziness, and others.

### Ethical Approval and Informed Consent

This study has been approved by the NCNP institutional review board. The initial protocol was approved on November 13, 2017, and the modified version was approved on March 5, 2019. Research coordinators will explain and obtain written informed consent from participants regarding the following items: objectives, reasons for enrollment, the methods and time period, potential burdens, predictable risks and benefits, handling of personal information, means for information storage and disposal, conflicts of interest, any potential invasiveness, and compensation for research-related injuries.

### Confidentiality

The administrator of the patients’ personal information will manage and store all research-related printed or electronic records with personal information, with a corresponding table of personal information and research identification numbers to prevent any information from being divulged, stolen, or lost. The details are described in Supplement 1.

## Discussion

This protocol described the design of our pilot study for testing the augmentation effect of inaudible high-frequency sounds on positive valence system–focused CBT. To date, treatments for depression and/or anhedonia do not guarantee clinically successful outcomes. In contrast to the studies of the augmentation effect of D-cycloserine on CBT for anxiety disorders,^44^ augmentation studies for CBT treatments of depression are limited. Exposure to inaudible high-frequency sounds does not require attentional or cognitive effort from either the patients or therapists; therefore, results from a future confirmative trial could indicate that cognitive behavioral therapy can be augmented in an effortless manner.

### Limitations

Our trial design has several limitations. First, this pilot trial aims to evaluate the potential efficacy of augmenting PoCot with inaudible high-frequency sounds. Because of its preliminary nature, this study only provides information regarding whether it is appropriate to proceed with a larger, definitive trial. Since our sample size calculation is specifically designed to obtain this information, the results of this trial should be cautiously interpreted. Second, considering the limited efficacy of traditional CBT approaches (eg, behavioral activation) and a promising novel neuroscience-driven treatment for anhedonia, we developed PoCot. However, the efficacy of this intervention has not been proven as a stand-alone treatment for anhedonia. Thus, further evidence is needed to test PoCot as a stand-alone treatment for anhedonia. A factorial design would be among the best methods to accomplish this because the use of inaudible high-frequency sound also has limited evidence for its efficacy as a stand-alone treatment for anhedonia. Third, we will not control for patient medications because this would present a potential recruitment barrier. Fourth, we included various outcome and process measures to evaluate the intervention from multiple perspectives; these evaluations should be interpreted as exploratory. Fifth, this trial cannot evaluate or offer detailed information for the following important aspects of the intervention: optimal doses or timing of PoCot and inaudible high-frequency sounds, the augmentation effect in each module of PoCot, specific subgroups that are responsive to PoCot and/or inaudible high-frequency sounds, and the influence of inaudible-high frequency sounds on several distinct reward processes.

### Conclusions

This trial is expected to provide initial findings on the synergistic effect of psychological interventions that target the positive valence system and use inaudible high-frequency sounds. The combination of CBT and sound therapy could have a synergistic effect on anhedonia.

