We hypothesized that the combination of the PoCot approach and inaudible high-frequency sounds would have a synergistic effect on anhedonia. Although, to our knowledge, no previous direct findings support this idea, PoCot is designed to enhance the brain reward circuity,^18,20^ while inaudible high-frequency sounds increase blood flow.^23^ In addition, reward circuity activation via inaudible high-frequency sounds leads to a relaxed attentional state.^27^ Considering that CBT is a learning process^28^ and positive emotions enhance the learning process,^29^ it is expected that a positive emotional state induced by inaudible high-frequency sounds will facilitate the learning process in CBT. Furthermore, inaudible high-frequency sounds are expected to enhance learning via EEG alpha-band power activation. The alpha-band frequency range inhibits activity in task-irrelevant brain regions, enabling effective task-irrelevant disengagement for information processing.^30^ In addition, inhibiting task-irrelevant memories coupled with alpha-band activity is believed to enhance semantic orientation, allowing individuals “to selectively access stored information that represents the meaning of sensory information and ‘higher order information,’ such as language, mathematics, and geography.”^31^^(p613)^ Hence, we expect that inaudible high-frequency sounds will augment the learning process of CBT via an induced relaxed attentional state and alpha band brain activity.

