### Interventions

#### Positive Valence System–Focused CBT

Both the intervention and control group will participate in PoCot, which will be conducted in a face-to-face, individualized format. Weekly sessions lasting 50 to 60 minutes will be conducted in a room with sound equipment. This intervention was developed using CBT advances that focus on the positive valence system,^18,19,20,21^ positive psychological interventions,^35^ positive emotion regulation interventions,^36^ traditional Japanese psychotherapy that emphasizes positive affect and reward,^37,38^ and findings from neuroscience and emotion research mentioned in the introduction.^29,39^ Biological and theoretical background information and details of the intervention are provided in the eAppendix and eTable in Supplement 2.

Early PoCot sessions will include psychoeducation that emphasizes the importance of the positive valence system for anhedonia treatment. The participants will then begin to practice savoring positive sensations and emotions and attentively monitoring positive events in daily life. Participants will be asked to identify thoughts that interrupt their mindful acceptance of positive sensations and emotions and to examine alternative thoughts. In parallel, the participants will be encouraged to identify their strengths and try to use them in daily life. To help identify strengths, participants will be asked to identify past positive memories.

The focus of the program will then gradually shift from enhancing the patient’s acceptance of short-term positive experiences (ie, short-term reward) to engaging longer-term, goal-directed, and more effortful behavior. Psychoeducation on the temporal discounting of rewards in anhedonia will be provided. The participants will be asked to identify longer-term goals or values in their lives. These goals will then be divided into smaller steps, and patients will be encouraged to engage in easier behaviors. Furthermore, patients will be asked to monitor events they are grateful for in daily life and to practice receiving and providing compliments to enhance positive interpersonal experiences. In the final session, participants will review the skills they acquired during the program and discuss how to maintain a positive lifestyle.

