#### Sound Material and Presentation System for Inaudible High-Frequency and Placebo Sounds

The intervention group will be exposed to inaudible high-frequency sounds during PoCot sessions. Rainforest sounds, a natural sound source containing the richest amount of high frequencies with a conspicuously fluctuating structure, were chosen as the sound source for this trial. Sounds containing inaudible high-frequency components (HFCs), referred to as *full-range sounds*, were recorded in the rainforest of Borneo from 2004 to 2009 using a high-speed, 1-bit coding signal processor in a direct stream digital format at a sampling frequency of 5.6 MHz. The electrical signal contains a wealth of HFCs (ie, >100 kHz). The sounds include animal and bird calls, insects chirping, and wind. The track is 47 minutes long and will be presented on repeat.

We selected PoCot without inaudible high-frequency sounds (ie, placebo sounds) as the comparator because previous studies successfully used placebo sounds as a comparator.^23,26^ There was almost no difference in the subjective experience of sound quality between inaudible high-frequency sounds and the placebo sounds. To generate placebo sounds, the inaudible HFCs were excluded from the original sound material using a low-pass filter (digital finite impulse response filter; cutoff frequency, 27 kHz; allowable passband ripple, 0.5 dB; stopband, 28 kHz-150 dB) using the MATLAB signal processing toolbox (MathWorks, Inc).

The level of audible sounds should not disturb conversations during PoCot, and the preferred sound level may vary depending on individual participants and therapists. Conversely, the inaudible HFCs should be presented equally to all participants in the intervention group. To this end, we constructed an original sound presentation system whereby the sound source signals recorded in a digital audio player (MR-2000S; KORG) can be divided into 2 pathways by a splitter with an independent volume control for each pathway (Behringer MX882; Behringer Music Group) (Figure 1). Using this presentation system, the fixed level of HFCs can be determined regardless of the audible low-frequency component level.

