### Objectives

#### Primary Objective

The primary objective of this trial is to compare the efficacy of PoCot with in-session exposure to inaudible high-frequency sounds vs PoCot with in-session exposure to placebo sounds on anhedonia symptoms. Anhedonia symptoms will be assessed by 44 patients who have been diagnosed with clinically significant anhedonia symptoms using the SHAPS.^40^

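### The article expects findings on a synergistic effect of PoCot and high-frequency sound, but with PoCot in both arms the trial can estimate only the add-on effect of the sound given PoCot

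*Protocol article*

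**What the plan says.** The last paragraph of the Introduction states the hypothesis: "We hypothesized that the combination of the PoCot approach and inaudible high-frequency sounds would have a synergistic effect on anhedonia". It supports this with an interaction mechanism: the sounds are expected to make learning within CBT easier, through mood, relaxed attention and alpha-band activity. The Conclusions return to it: "This trial is expected to provide initial findings on the synergistic effect of psychological interventions that target the positive valence system" and that use the sounds. A second sentence there says that the combination could have such an effect.

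The design and analysis sections describe something narrower:

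- Positive Valence System–Focused CBT: "Both the intervention and control group will participate in PoCot".
- Sound Material and Presentation System: "We selected PoCot without inaudible high-frequency sounds (ie, placebo sounds) as the comparator".
- Primary Objective: to "compare the efficacy of PoCot with in-session exposure to inaudible high-frequency sounds vs PoCot with in-session exposure to placebo sounds on anhedonia symptoms".
- Outcome Analysis: "The treatment effects will be presented as the difference in adjusted means between the allocations at week 12".

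The Abstract (Findings), Sample Size, the opening of the Discussion and the first limitation all describe the target as augmentation. The second limitation says that PoCot is unproven as a stand-alone treatment and that stand-alone evidence for the sounds is limited. On testing PoCot alone it adds: "A factorial design would be among the best methods to accomplish this". No section says that interaction cannot be tested in this trial.

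**The concern.** Synergy is a claim about departure from additivity. To see it, one must know what the sound does without PoCot and compare that with what it does alongside PoCot. This trial has no arm without PoCot, so the quantity named in the hypothesis and the Conclusions is not one that the data can inform.

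At stake is how a positive result is read. The Introduction argues from earlier studies that the sounds alone, without any CBT, act on reward circuitry and improve comfort and approach behavior. A benefit of the sound that has nothing to do with PoCot is therefore a live explanation on the article's own account. It would produce the same result as the interaction mechanism, and a reader guided by the Conclusions could credit the wrong one.

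**Working it through.** **Inputs.** Two arms, 1:1 (Trial Design). PoCot in both arms, with sound against placebo sound (Interventions, Primary Objective). One adjusted mean difference in SHAPS at week 12, two-sided 0.05 (Outcome Analysis). Standardized effect 0.2 to 0.3 and main-trial total of 344 to 786 (Sample Size). Power is not stated in the article; 80% is assumed here.

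**Step 1: which quantity was the main trial sized for?** For two means with SD 1, n per arm = 2(1.960 + 0.842)² / d².

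- d = 0.2: 393 per arm, 786 in total. The article's 786 is reproduced exactly.
- d = 0.3: 175 per arm, 350 in total, against the article's 344 (1.7% apart).

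The planning figures are those of a simple two-arm add-on contrast.

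**Step 2: what the contrast contains.** Let P = 1 with PoCot, S = 1 with high-frequency sound and S = 0 with placebo sound. Score improvement as positive:

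mean(P, S) = b0 + bP·P + bS·S + bPS·P·S

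- Observed: mean(1,1) − mean(1,0) = bS + bPS.
- Synergy: bPS = [mean(1,1) − mean(1,0)] − [mean(0,1) − mean(0,0)].

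The second bracket needs two cells that the trial does not have. With a contrast of 0.30 SD, the upper end of the article's range, used for illustration:

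| Case | Sound alone (bS) | Interaction (bPS) | Expected contrast |
|---|---|---|---|
| Purely additive | 0.30 | 0 | 0.30 |
| Half and half | 0.15 | +0.15 | 0.30 |
| Pure synergy | 0 | +0.30 | 0.30 |
| Antagonism | 0.50 | −0.20 | 0.30 |

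All four give the same expected data in both arms. More patients narrow the interval around 0.30 but do not tell the rows apart.

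**Step 3: does another planned analysis help?** The mixed model has an allocation-by-visit interaction, but that concerns time, and all patients receive PoCot throughout. The moderation, mediation and homework-adherence analyses (Secondary Objectives) are run within the same two arms. None adds a cell without PoCot. The contrast would equal synergy only if the sound alone were known to do nothing. The article does not say so: it calls the stand-alone evidence limited, and the Introduction argues for an effect.

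**Step 4: scale of the difference, for illustration only.** In a balanced 2×2 factorial with SD 1, the interaction contrast has variance 4/n with n per cell, so n = 4(1.960 + 0.842)² / d².

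- d = 0.3: 349 per cell, 1,396 in total.
- d = 0.2: 785 per cell, 3,140 in total.

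That is about four times the two-arm totals of 350 and 786. An interaction and an add-on effect are different targets.

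**The case against.** The best defense is that the word drives nothing. The objective, sample size, estimate and most of the framing concern augmentation, and the Introduction's own argument ends by speaking of the sounds augmenting CBT learning. On this view *synergistic* is a loose synonym. The trial is also a declared exploratory pilot, and the Limitations ask for cautious reading and already mention a factorial design because separate evidence on each component is thin.

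Much of this stands, and it rules out three stronger readings that a reader might infer:

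- *That the article promises to demonstrate synergy.* It does not. It speaks of initial findings and of what the combination could do.
- *That the primary comparison is flawed.* It is not. It is a valid randomized estimate of the sound's add-on effect given PoCot.
- *That the confirmatory trial will be aimed at an untested mechanism.* The Abstract (Meaning) directs future trials at the augmentation effect, which is what this pilot estimates.

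What does not stand is the synonym argument. The Introduction attaches a specific interaction mechanism to the word, so readers have reason to take it literally. The factorial remark is tied to stand-alone efficacy. The fifth limitation lists what the trial cannot evaluate without naming interaction, and the Conclusions then restate the synergy claim. Pilot status excuses imprecision, but here the quantity is not identified at all.

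**Conclusion.** The concern holds as a point of interpretation. The Introduction hypothesizes synergy and the Conclusions expect initial findings on it, while the two-arm design yields only the augmentation effect of the sound given PoCot. The trial carries no information on how that effect divides between the sound's own action and an interaction, whatever the sample size.

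This rests on reading synergy as departure from additivity on the SHAPS scale. It needs no assumption about effect size or power; the 0.30 SD cases and the factorial totals only illustrate it. Allocation, sample size and primary analysis are unaffected. It is an internal inconsistency that should be corrected because it changes what the trial may claim.

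**What to change.** 1. In the hypothesis sentence of the Introduction and in both sentences of the Conclusions, replace the synergy wording with: augmentation (add-on) effect of high-frequency sound given PoCot.
2. In the Limitations, add a sentence such as: Because both arms receive PoCot, this two-arm design cannot test interaction between PoCot and the sounds; doing so would need arms without PoCot, for example in the factorial design mentioned above.

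The cost is wording only: no change to arms, sample size, data collection or analysis. The claim becomes more modest and agrees with the rest of the article.
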